### Stopping criteria

Assuming a test with 90% sensitivity, a 99% specificity, and a pre-test probability (prevalence) of 30%, we would require 200 participants to meet the minimum thresholds as stated above. This would also mean that tests with more than seven false negatives or two false positives could be immediately dropped from the study. This allows us to exclude tests with sensitivities of 50%, 60%, 70%, or 80% after the first 50, 60, 80, and 120 participants recruited. For tests with poor specificities of 80%, 85%, 90%, or 95% these would be identified after 15, 20, 30, and 60 participants recruited. The prevalence of COVID-19 affects the sample size required. With a pre-test probability (prevalence) of 5% we would require 1200 participants to evaluate a POCT and interim futility analyses will stop the evaluation after seven false negatives or twelve false positives. POCTs with an actual sensitivity of 50%, 60%, 70%, or 80% would reach futility criteria after the first 280, 350, 470, and 700 participants. POCTs with an actual specificity of 80%, 85%, 90% or 95% would reach futility criteria after the first 65, 85, 130, and 255 recruited participants.

Evaluations of the first POCTs will be performed without implementation of stopping criteria to establish whether sufficient information to create the composite reference standard can be obtained sufficiently quickly to make these criteria viable. The figures presented here should therefore be regarded as indicative for a POCT designed to detect active infection and will be reviewed once this information becomes available.

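### The recruitment counts given as exclusion points for poor tests are expected-value points, with only a 35–48% chance of exclusion by then under the 30% prevalence rule as worded

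*Protocol article*

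**What the plan says.** The Stopping criteria section of the protocol article gives two worked examples.

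- **30% prevalence.** For a test with 90% sensitivity and 99% specificity, "we would require 200 participants to meet the minimum thresholds as stated above". The limit is that "tests with more than seven false negatives or two false positives could be immediately dropped from the study". The section concludes that this makes it possible to "exclude tests with sensitivities of 50%, 60%, 70%, or 80% after the first 50, 60, 80, and 120 participants", and adds: "For tests with poor specificities of 80%, 85%, 90%, or 95% these would be identified after 15, 20, 30, and 60 participants recruited".
- **5% prevalence.** The sample is 1200 and "interim futility analyses will stop the evaluation after seven false negatives or twelve false positives". Tests with sensitivities of 50–80% "would reach futility criteria after the first 280, 350, 470, and 700 participants". Those with specificities of 80–95% are said to do so after 65, 85, 130 and 255.

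No probability is attached to any count, and none is described as an average. The section ends by calling the figures indicative. The reason given is that it is not yet known whether information for the composite reference standard will arrive quickly enough. The first evaluations will run without stopping criteria.

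**The concern.** A reader takes the counts as the recruitment by which a poor test will have been dropped. Each is in fact close to the point where the average number of errors equals the limit, and chance variation leaves a large share of poor tests still under evaluation there. There is a second slip at 30% prevalence. The rule as worded requires more than seven false negatives or more than two false positives, yet the counts are computed for seven and two, so they are too low even as averages.

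The stake is a stated operating property. The Number of participants section presents the thresholds as a basis for identifying poor tests early, and the Strengths and limitations section names the stopping criteria as a strength. The printed counts are the only description of how early that identification would come.

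**Working it through.** **Inputs**, all from Stopping criteria: prevalence 30% or 5%; the listed sensitivities and specificities; the limits; the stated counts; full samples of 200 and 1200.

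**Error rate per participant.** False negatives: prevalence × (1 − sensitivity). False positives: (1 − prevalence) × (1 − specificity).

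**Step 1: reproduce the stated counts as limit ÷ rate.**

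- 30%, limit 7: 7/0.15 = 46.7, 7/0.12 = 58.3, 7/0.09 = 77.8, 7/0.06 = 116.7. Stated: 50, 60, 80, 120.
- 30%, limit 2: 2/0.14 = 14.3, 2/0.105 = 19.0, 2/0.07 = 28.6, 2/0.035 = 57.1. Stated: 15, 20, 30, 60.
- 5%, limit 7: 7/0.025 = 280, 7/0.02 = 350, 7/0.015 = 467, 7/0.01 = 700. Stated: 280, 350, 470, 700.
- 5%, limit 12: 12/0.19 = 63, 12/0.1425 = 84, 12/0.095 = 126, 12/0.0475 = 253. Stated: 65, 85, 130, 255.

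All 16 match after rounding, so the counts are expected-value points.

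**Step 2: probability of exclusion by the stated count.** With X ~ Binomial(n, rate), the 30% rule as worded fires at X ≥ 8 false negatives or X ≥ 3 false positives. The inclusive column uses X ≥ 7 or X ≥ 2. The last three columns apply to the rule as worded.

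| 30% prevalence | n stated | Expected errors | P, as worded | P, inclusive | Mean n to trigger | Median n | n for 90% |
|---|---|---|---|---|---|---|---|
| Sens 50% | 50 | 7.5 | 48.1% | 63.9% | 53 | 51 | 77 |
| Sens 60% | 60 | 7.2 | 43.3% | 59.1% | 67 | 64 | 96 |
| Sens 70% | 80 | 7.2 | 43.2% | 58.8% | 89 | 85 | 129 |
| Sens 80% | 120 | 7.2 | 43.2% | 58.5% | 133 | 128 | 194 |
| Spec 80% | 15 | 2.1 | 35.2% | 64.2% | 21 | 19 | 37 |
| Spec 85% | 20 | 2.1 | 35.2% | 63.6% | 29 | 26 | 49 |
| Spec 90% | 30 | 2.1 | 35.1% | 63.1% | 43 | 38 | 75 |
| Spec 95% | 60 | 2.1 | 35.1% | 62.5% | 86 | 77 | 151 |

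The mean to trigger is 8 ÷ rate or 3 ÷ rate, for example 8/0.15 = 53 and 3/0.14 = 21.

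| 5% prevalence | n stated | P, as worded (≥7 FN, ≥12 FP) | P if limit must be exceeded | Median n, as worded | n for 90%, as worded |
|---|---|---|---|---|---|
| Sens 50% | 280 | 55.2% | 40.1% | 267 | 420 |
| Sens 60% | 350 | 55.2% | 40.1% | 334 | 525 |
| Sens 70% | 470 | 55.9% | 40.9% | 445 | 700 |
| Sens 80% | 700 | 55.1% | 40.1% | 667 | 1051 |
| Spec 80% | 65 | 59.4% | 46.8% | 62 | 85 |
| Spec 85% | 85 | 56.1% | 43.8% | 82 | 114 |
| Spec 90% | 130 | 58.5% | 46.6% | 123 | 172 |
| Spec 95% | 255 | 55.4% | 43.7% | 246 | 347 |

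**Step 3: robustness at 30%.** Fixing the numbers of infected and uninfected participants at their expected values gives 32–50%. Letting either limit trigger, with the other accuracy measure at its design value, gives 35–48%.

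**Step 4: exclusion by the full sample, limits as worded.**

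- 30%, 200 participants: 91.7% for 80% sensitivity, 97.2% for 95% specificity, at least 99.8% for the worse tests.
- 5%, 1200 participants: 95.5% for 80% sensitivity, at least 99.9% for the rest.

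**The case against.** The strongest reply is that the counts are fair guides to typical timing. At 5% prevalence every median stopping point is slightly earlier than the stated count, and for sensitivity at 30% the medians (51, 64, 85, 128) are only a little later. This stands. Only the specificity set at 30% is clearly off, with medians of 19, 26, 38 and 77 against 15, 20, 30 and 60. But the text presents the counts as points of exclusion or identification, not as typical points.

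A second reply is that the limits may be meant inclusively, since the 5% example is worded that way. That is a fair ambiguity, but it lifts the 30% probabilities only to about 59–64%.

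A third is that the figures are called indicative, will be reviewed, and do not apply to the first evaluations. Tests are also dropped on error counts, not on recruitment counts. This lowers the consequence. It does not cure the statement, because the caveat concerns the speed of composite-reference information and says nothing of chance variation. Nor is this a detail left to the SAP: the counts are printed here.

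A reader might go further and infer that the rule seldom removes poor tests, or that there is practically no early exclusion. The figures do not support this. The 194 of 200 for an 80%-sensitive test is a 90% figure for the borderline case, since 80% is the protocol's own example of a minimum sensitivity; 68% of such tests are gone by 150 participants. Nor does the document say that these counts drive resource planning, or that early exclusion is its main strength.

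**Conclusion.** The point holds as an error in the claimed timing. The Stopping criteria section presents expected-value points as exclusion points. Under the 30% rule as worded, exclusion by those points has probability 43–48% (sensitivity) and 35% (specificity). Under the 5% rule as worded it is 55–59%. No reading of the limits brings exclusion by the stated counts above about 64%. The rule's eventual ability to drop these tests is not in question, and the error does not alter how accuracy will be estimated.

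The calculation assumes independent participants, true prevalence equal to the stated value, errors counted against the reference standard, and reference results available at once. Any delay in those results would push the exclusion points later.

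**What to change.** Rewrite the counts in one of two ways.

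1. Label them as expected points with roughly even odds of exclusion, and recompute the 30% set for the limit as worded: about 53, 67, 89 and 133 participants for the 8th false negative, and 21, 29, 43 and 86 for the 3rd false positive.
2. Give counts at a stated probability. At 90% these are 77, 96, 129, 194 (sensitivity) and 37, 49, 75, 151 (specificity) for 30% prevalence, and 420, 525, 700, 1051 and 85, 114, 172, 347 for 5%. The 90% level is a choice; for 80%, the 30% counts are 67, 84, 113, 169 and 30, 40, 60, 122.

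In either case, state whether a test is dropped on reaching the limit or on exceeding it, and use the same wording in both examples. If the limits or their wording change, recompute the counts.

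The cost is one rewritten paragraph, with figures less favourable than those now printed. The design does not change.

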### Number of participants

We have calculated sample sizes using standard methodology based on minimum clinically relevant sensitivity or specificity (whichever is the most critical for the intended placement in the care pathway), not expected values from preliminary work [16]. For example, acceptable thresholds for minimum sensitivity and specificity of 80% and 95% respectively, can be used to determine sample size requirements and a strategy for early identification of poorly performing tests.

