A strength of the RAPTOR-C19 protocol is the stopping criteria to identify POCTs that have already exceeded the maximum number of false positives or false negatives necessary to be able achieve the target sensitivity and specificity. A corresponding weakness is that a test which has focussed on achieving high sensitivity but has low specificity may be disadvantaged in a low prevalence setting, especially if the anticipated prevalence used to set the stopping criteria, was higher than the actual prevalence. In this circumstance, tests may be excluded from the analysis because of accumulating too many false positive results in comparison to the laboratory and composite reference standards. Nevertheless, these stopping criteria reflect MHRA mandated performance criteria. During early evaluations we will establish whether sufficient information to create the composite reference standard can be obtained sufficiently quickly to make stopping criteria viable.

We recognise the challenges of recruitment in a changing policy environment, with variable disease prevalence. GP sites will be recruited from the RCGP Research and Surveillance Centre (RSC) is an internationally renowned source of information, analysis, and interpretation of primary care data [40]. The dataset is nationally representative [41], having only small differences with the national population, which have now been quantified and can be assessed for clinical relevance for specific studies. With twice weekly data extractions, the dataset is one of the most up to date in the UK, and now a platform within ORCHID. ORCHID is in the process of enhancing the frequency of extraction and scope of data linkage. It is already extracting primary care computerised medical records (CMRs) daily and linking with linked hospital data and mortality data. ORCHID will additionally support RAPTOR-C19 by allowing patient follow-up within the RCGP RSC network, and the creation of an enhanced composite reference standard to overcome limitations of laboratory reference tests [30].

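### In the 5%-prevalence illustration, the limit of twelve false positives is the count expected from a 99%-specific test, not the maximum compatible with the stated 95% minimum specificity

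*Protocol article*

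**What the plan says.** All references are to the protocol article.

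- *Number of participants* bases the sample sizes on minimum clinically relevant values rather than expected ones. It gives as an example "acceptable thresholds for minimum sensitivity and specificity of 80% and 95% respectively", and links these minima to the early removal of poor tests.
- *Stopping criteria*, higher-prevalence illustration: "Assuming a test with 90% sensitivity, a 99% specificity, and a pre-test probability (prevalence) of 30%, we would require 200 participants". Here "tests with more than seven false negatives or two false positives could be immediately dropped from the study".
- *Stopping criteria*, lower-prevalence illustration: at 5% prevalence the required number rises to 1200. For this case the section states that "interim futility analyses will stop the evaluation after seven false negatives or twelve false positives". The consequence is given as "POCTs with an actual specificity of 80%, 85%, 90% or 95% would reach futility criteria after the first 65, 85, 130, and 255 recruited participants".
- The same section then says that the first tests will be evaluated without stopping, and that the figures are indicative and will be reviewed.
- *Strengths and limitations* presents the rule as a strength because it identifies tests that "have already exceeded the maximum number of false positives or false negatives necessary to be able achieve the target sensitivity and specificity". It concedes that a test of low specificity may be disadvantaged at low prevalence, particularly when actual prevalence falls below the anticipated figure.
- *Summary statistics of diagnostic accuracy* specifies exact 95% confidence intervals.

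**The concern.** A futility limit of the kind described in *Strengths and limitations* should sit at the largest error count that still lets a test meet the minimum. In the 5% illustration the false-positive limit appears to be tied to the 99% specificity assumed for a good test. Tests with specificity comfortably above 95% would then be dropped as futile although they could still meet the criterion. The output of this rule is a decision to stop evaluating a test, so a miscalibrated limit would discard acceptable tests and describe them as unable to reach the target.

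**Working it through.** **Inputs** (*Number of participants*; *Stopping criteria*): minimum specificity 95%; assumed specificity 99%; prevalence 5%; N = 1200; limit 12 false positives (FP). Reference-negatives: 1200 × 0.95 = 1140.

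**1. Reproducing the plan's stopping points.** Expected participants until the limit is reached = 12 / [(1 − specificity) × 0.95].

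| Specificity | Computed | Stated |
|---|---|---|
| 80% | 63.2 | 65 |
| 85% | 84.2 | 85 |
| 90% | 126.3 | 130 |
| 95% | 252.6 | 255 |

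The stated figures follow from 12 with upward rounding, so the limit is not a misprint. Stopping at the 13th FP would give 13 / (0.20 × 0.95) = 68.4 for the first row, so the rule appears to act at the 12th.

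**2. Where twelve sits.** Expected FP for a 99%-specific test: 1140 × 0.01 = 11.4, rounded up to 12. Expected FP for a 95%-specific test: 1140 × 0.05 = 57.

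**3. Is 95% out of reach at twelve?** Observed specificity is 1128/1140 = 98.9%, with exact (Clopper-Pearson) 95% lower limit 98.17%. The largest FP count compatible with 95% depends on how passing is defined:

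- exact lower limit: 42 (95.05%; 43 gives 94.95%); the Wilson limit also gives 42
- Wald lower limit: 44
- point estimate alone: 57

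Twelve is far below all of them.

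**4. Chance of being stopped by 1200 participants.** FP counts only increase, so the probability of hitting the limit at any time equals the binomial tail of the final count, X ~ Bin(1140, 1 − specificity).

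| True specificity | Expected FP | P(X ≥ 12) | P(X ≥ 13) | P(X ≥ 43) |
|---|---|---|---|---|
| 95% | 57.0 | 1.000 | 1.000 | 0.979 |
| 96% | 45.6 | 1.000 | 1.000 | 0.674 |
| 97% | 34.2 | 1.000 | 1.000 | 0.078 |
| 98% | 22.8 | 0.995 | 0.990 | 0.0001 |
| 98.5% | 17.1 | 0.920 | 0.872 | <0.0001 |
| 99% | 11.4 | 0.469 | 0.355 | <0.0001 |
| 99.5% | 5.7 | 0.014 | 0.006 | <0.0001 |

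The P(X ≥ 13) column covers the lenient reading, in which stopping needs more than twelve. Letting the number of reference-negatives vary around 1140 changes P(X ≥ 12) by no more than 0.0001.

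**5. Stopping points if the limit were the 43rd FP.** 43 / [(1 − specificity) × 0.95] = 226, 302, 453 and 905 participants at 80%, 85%, 90% and 95%. Each is 43/12 ≈ 3.6 times the corresponding value for twelve.

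**The case against.** The strongest defence is the status of the figures. They are labelled indicative, the first tests run without stopping, the 80%/95% minima are introduced as an example, and each new test needs its own protocol amendment. This stands as a limit on urgency: no test is rejected by this number today. It does not remove the inconsistency. The reason given for the review is whether composite-standard information arrives quickly enough, and such a review could leave the limit untouched.

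The concession in *Strengths and limitations* does not cover the case either. It concerns tests of low specificity, chiefly when prevalence is lower than anticipated. Here tests at 97% to 98.5% are stopped at exactly the anticipated prevalence.

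Four stronger readings are tempting, and the article does not support them.

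- *The 30% rule was calibrated to the 95% minimum and only the 5% rule went astray.* Both limits equal the 1% expected count rounded up (140 × 0.01 = 1.4, giving 2). With 2 of 140 the exact lower limit is 94.9% and the Wald limit 96.6%, so the closeness to 95% depends on the interval and does not reveal the rule.
- *The correct limit must be 43.* No section defines passing by an exact lower limit; exact intervals are specified only for reporting. The false-negative limit of 7 in 60 does not follow that rule: its exact lower limit is 77.4%, and only the Wald limit (80.2%) clears 80%.
- *The overall chance of wrongly stopping a 90%/99% test measures this fault.* That figure also contains the false-negative limit, which alone stops a 90%-sensitive test 39% of the time and is a separate matter.
- *5% is the setting the platform expects.* It is one illustration. The article describes recruiting symptomatic patients and using COVID-19 hubs to raise prevalence above background.

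**Conclusion.** The point holds for the 5% illustration. The limit of twelve false positives contradicts the 95% minimum in *Number of participants*. It also makes the description in *Strengths and limitations* untrue for this scenario, because a test stopped at twelve can still finish with an exact lower limit of 98.2%. The effective hurdle is near 98–99%. Tests with true specificity of 98% or less are stopped at least 99% of the time, and those at 98.5% 92% of the time. A test with exactly the assumed 99% is stopped 47% of the time (36% if more than twelve is required). Near-certain stopping should not be inferred for tests at 99% or better; at 99.5% the probability is 1.4%.

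The probabilities assume 1140 reference-negatives, independent results and specificity measured against the reference standard as given. That twelve falls short of the maximum does not depend on the choice of interval. The exact replacement value does.

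**What to change.** Reconcile the false-positive limit with the 95% minimum and state the rule that produces it.

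- **If 95% stands** and passing means that the exact 95% lower limit exceeds 95%, the maximum is 42 false positives among 1140 reference-negatives, with stopping at the 43rd. Under a Wald limit the maximum is 44. Tie the limit to the number of reference-negatives rather than to total recruitment, so that a shift in prevalence does not change its meaning. Restate the stopping points as about 226, 302, 453 and 905 participants in place of 65, 85, 130 and 255.
- **If a hurdle near 98–99% is intended** at low prevalence, say so in *Number of participants* and *Strengths and limitations*, and report the chance of stopping a test whose true specificity is 99%.

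Either way, add calibration of the limits to the planned review, and say whether stopping occurs at the limit or only beyond it.

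The change is one of wording in the protocol and analysis plan. The first option has a real operating cost: poorly specific tests are stopped about 3.6 times later, which weakens early removal of poor tests. Under it, a test at exactly 95% is still stopped about 98% of the time by 1200 participants, and a test at 98% about 0.01% of the time.

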### Illustrative sample sizes

Table 5 presents illustrative sample sizes to achieve a range of POCT sensitivities based on a standard error of 2.5%. A standard error of 2.5% will give a confidence interval of 5% on either side of the sensitivity estimate.

**Table 5 Tab5:** Illustrative sample sizes to achieve a range of POCT sensitivities based on a standard error of 2.5%

	Prevalence	40%	35%	30%	25%	20%	15%	10%	5%
**Sensitivity**	**95%**	190	218	254	304	380	507	760	1520
	**90%**	360	412	480	576	720	960	1440	2880
	**85%**	510	583	680	816	1020	1360	2040	4080
	**80%**	640	732	854	1024	1280	1707	2560	5120
	**75%**	750	858	1000	1200	1500	2000	3000	6000
	**70%**	840	960	1120	1344	1680	2240	3360	6720

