### Summary statistics of diagnostic accuracy

Sensitivity, specificity, and positive and negative predictive values for each POCT will be calculated with exact 95% confidence intervals.

For the primary outcome and first secondary outcome:

For consecutive POCTs for active infection, the diagnostic accuracy of each POCT will be summarised independently using 2 × 2 tables for POCT (+/-) and the current standard PHE reference test (+/-) for active infection. For consecutive POCTs for past infection, the diagnostic accuracy of each POCT will be summarised independently using 2 × 2 tables for POCT (+/-) and the current standard PHE reference test (+/-) for past infection. Measures of diagnostic accuracy will also be presented adjusted for imperfect reference standard bias, using the best available estimate of the accuracy of the PHE reference test.

For the second and third secondary outcomes:

For consecutive POCTs for active infection, the enhanced diagnostic accuracy of each POCT will be summarised independently using 2 × 2 tables for POCT (+/-) and the composite reference standards as outlined in Table 4 (+/-). For consecutive POCTs for past infection, the enhanced diagnostic accuracy of each POCT will be summarised independently using 2 × 2 tables for POCT (+/-) and the composite reference standards (+/-) for past infection.

Results for the primary outcome will be stratified by adults vs children, by age group (< 16, 16–40, 40–60, 60+ years), by gender, by ethnicity and by spectrum of disease (a combined measure of symptom severity and duration). A further subgroup analysis will test for differences in diagnostic performance by practice, and if any differences are detected, associations with practice size, location and model of care will be explored.

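### Table 5's stated precision of 5 points on either side is a normal-approximation figure; under the planned exact intervals the lower arm is about 7.4 points at 95% sensitivity and 6.1 at 90%

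*Protocol article*

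**What the plan says.** Under Illustrative sample sizes, the protocol article gives "illustrative sample sizes to achieve a range of POCT sensitivities based on a standard error of 2.5"%, for sensitivities of 70% to 95% and prevalences of 5% to 40%. It then states the resulting precision without qualification: "A standard error of 2.5% will give a confidence interval of 5% on either side of the sensitivity estimate".

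Under Summary statistics of diagnostic accuracy it fixes the interval method: "Sensitivity, specificity, and positive and negative predictive values for each POCT will be calculated with exact 95% confidence intervals". The abstract repeats the commitment to exact intervals.

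Nothing beside Table 5 says that the 5 points come from a normal approximation or that the reported intervals will have unequal arms.

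**The concern.** The precision sentence and the analysis method describe different intervals. A standard error multiplied by about 2 gives equal arms around the estimate. An exact binomial interval for a proportion well above one half has a longer lower arm and a shorter upper arm, and the imbalance grows as the proportion nears 100% and the number of cases falls. The 95% row of Table 5 has both the highest sensitivity and the fewest cases.

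At stake is what a reader expects from a chosen cell. Someone sizing an evaluation of a highly sensitive test from Table 5 would expect a lower limit about 5 points under the estimate, and the planned analysis would give one further away. When a test is judged against a minimum sensitivity, the lower side is the informative one.

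**Working it through.** **Inputs.** Standard error 0.025, and the sensitivities, prevalences and cell values of Table 5 (Illustrative sample sizes). Interval method: exact 95% (Summary statistics of diagnostic accuracy), taken here as Clopper-Pearson.

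**Step 1: reproduce the table.** Cases = Se(1 − Se)/0.025²; participants = cases/prevalence.

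- Se 95%: 0.95 × 0.05/0.000625 = 76 cases; at 30% prevalence 76/0.30 = 253.3 (table 254); at 5%, 76/0.05 = 1520 (table 1520).
- Se 90%: 0.90 × 0.10/0.000625 = 144 cases; at 30%, 144/0.30 = 480 (table 480).
- Se 85%, 80%, 75% and 70%: 204, 256, 300 and 336 cases.

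All 48 cells agree within one participant.

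**Step 2: reproduce the 5 points.** 1.96 × 2.5 = 4.9, rounded to 5. This is a Wald half-width and is the same in every row.

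**Step 3: exact limits at the same case numbers.** For x positives among n cases, the lower limit is the 2.5% quantile of Beta(x, n − x + 1) and the upper limit is the 97.5% quantile of Beta(x + 1, n − x). With n = 76 the two attainable results nearest 95% are:

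- 72/76 = 94.7%: 87.1% to 98.5%, which is 7.7 below and 3.8 above.
- 73/76 = 96.1%: 88.9% to 99.2%, which is 7.2 below and 3.1 above.

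Averaging each arm over x ~ Binomial(n, Se):

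| Sensitivity | Cases | Wald arm | Exact, below | Exact, above |
|---|---|---|---|---|
| 95% | 76 | 4.9 | 7.4 | 3.5 |
| 90% | 144 | 4.9 | 6.1 | 4.3 |
| 85% | 204 | 4.9 | 5.6 | 4.6 |
| 80% | 256 | 4.9 | 5.4 | 4.7 |
| 75% | 300 | 4.9 | 5.3 | 4.8 |
| 70% | 336 | 4.9 | 5.2 | 4.8 |

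Wilson limits in the 95% row give lower arms of 7.5 (72/76) and 7.0 (73/76), so the result is not just Clopper-Pearson conservatism.

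**Step 4: cases needed for a 5-point exact lower arm.**

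- Se 95%: 142 cases if the observed sensitivity is exactly 95%, or 139 if the average lower arm is to be 5 points.
- Se 90%: 202 and 200 cases on the same two criteria.

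In round figures this is 140 and 200 cases, against 76 and 144. At 30% prevalence: 140/0.30 ≈ 467 and 200/0.30 ≈ 667 participants, against 254 and 480 in the table.

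**Step 5: effect on a comparison with 80%.** At the Table 5 case numbers, the probability that the exact lower limit exceeds 80% is 98.7% in the 95% row and 91.7% in the 90% row.

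**The case against.** The strongest reply is that this is ordinary planning practice. Quoting a standard error signals a normal approximation, the table is called illustrative in its heading, text and caption, and every cell is right for the standard error it uses. The total exact width is also not far from the 10 points implied: on average 10.9 points in the 95% row and 10.0 to 10.4 in the others. The interval is mostly shifted downwards rather than widened. In the rows at 80% sensitivity and below, a lower arm of 5.2 to 5.4 points rounds to the stated whole number.

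Most of that stands, and it limits the point to one sentence and two rows. It does not rescue the sentence, because the word illustrative describes the sample sizes, whereas the precision is asserted as a consequence and differs from what the stated method will deliver.

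Two stronger readings are tempting and are not supported:

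- A reader might infer that Table 5 is the basis on which each test's recruitment is set. The article does not say so. Under Stopping criteria it gives separate sizes, 200 participants at 30% prevalence and 1200 at 5% for a test with 90% sensitivity. These differ from Table 5's 480 and 2880.
- A reader might infer that good tests would wrongly miss an 80% minimum. The article gives 80% as an example threshold under Number of participants, and it nowhere states a rule comparing the exact lower limit with it. Even under such a rule, step 5 shows that tests in the 95% and 90% rows would usually clear it.

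**Conclusion.** The point holds as a minor one. The stated precision belongs to an interval that the protocol does not plan to report. The understatement of the lower arm is material at 95% sensitivity (7.4 points instead of 5), moderate at 90% (6.1), small at 85% (5.6) and negligible at 80% and below. The upper arm is shorter than 5 points on average in every row, so the discrepancy is on the lower side only. The sample sizes themselves are not in error.

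This rests on reading exact as Clopper-Pearson and on the number of reference-positives equalling its expected value. That number will vary in practice, which adds further uncertainty.

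**What to change.** Keep the Table 5 sizes. Replace the precision sentence with the expected exact lower and upper arms for each row (95%: −7.4/+3.5; 90%: −6.1/+4.3; 85%: −5.6/+4.6; 80%: −5.4/+4.7; 75%: −5.3/+4.8; 70%: −5.2/+4.8), and add that they assume the expected number of reference-positive participants. This costs one sentence or two extra columns and changes no analysis, stopping criterion or recruitment figure.

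If a 5-point exact lower arm is really what is wanted, recompute the table on that criterion and state the criterion. The 95% and 90% rows would then need about 140 and 200 cases, with participant numbers rising in proportion.
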